**Figure 1 figure1:**
[figure not shown]
Graphical overview of the study procedures. The cubes are used to illustrate the randomization process (variable block randomization (ie, block sizes=4, 6, 8) with a 1:1 allocation ratio stratified by sex and per institute (study center), as described in section “Methods–Randomization”).

### Recruitment

Older adults with mNCD will be recruited between May 2022 and September 2023 in collaboration with (memory) clinics in a larger area of Zurich and St. Gallen. Suitable patients will either be identified from medical records and patient registries of (memory) clinics, or from recent diagnostics performed by medical doctors or therapists authorized to search for medical records. Alternatively, suitable patients will be identified by an informant (ie, health care professionals) based on suspicion of MCI in one of their patients (see *Methods—Eligibility Criteria* section). Identified patients will be verbally informed about the study and will receive leaflets by their physicians or therapists containing key information about study participation and researchers’ contact details. If patients are interested in being informed about the study in detail, they will be asked to provide consent to share their contact details with the research team and will be contacted by phone or email by a trained investigator of the study team. In case of initial interest in participating in the study, all interested subjects will be fully informed about the study procedures in-person (at the interested persons’ home or at one of the study centers, depending on their preferences) by providing verbal explanations and an information sheet. After sufficient time for consideration (ie, at least 24 hours after handing out the study information sheet, but on average around 1 week), suitable patients willing to participate in the study will provide written informed consent in a second in-person meeting with one of the trained investigators of the study team at the home of the interested persons or at one of the study centers. After providing written informed consent, participants will be fully screened for eligibility (see section “Methods—Eligibility Criteria”), and premeasurements will be scheduled.

### Eligibility Criteria

All eligibility criteria are detailed in Textbox 1.

Description of all eligibility criteria.Inclusion criteriaParticipants fulfilling all the following inclusion criteria were eligible:(1=mild neurocognitive disorder) clinical diagnosis of “mild neurocognitive disorder” according to International Classification of Diseases 11th Revision [13] or Diagnostic and Statistical Manual of Mental Disorders 5th Edition [12] OR (2=screened for mild cognitive impairment [sMCI]) patients sMCI according to the following criteria: (1) informant (ie, health care professional)-based suspicion of MCI confirmed by (2) an objective screening of MCI based on the German version of the using the quick mild cognitive impairment screen [96] with (2A) a recommended cut-off score for cognitive impairment (MCI or dementia) of <62/100 [97], while (2B) not falling below the cut-off score for dementia (ie<45/100 [97]).Speaking GermanAble to stand at least for 10 minutes without assistanceExclusion criteriaThe presence of any of the following criteria led to exclusion:Mobility impairments (ie, gait and balance) that prevent experiment participationPresence of additional, clinically relevant (ie, acute or symptomatic or both) neurological disorders (ie, epilepsy, stroke, multiple sclerosis, Parkinson’s disease, brain tumors, or traumatic disorders of the nervous system)Presence of any other unstable or uncontrolled diseases (eg, uncontrolled high blood pressure and progressing or terminal cancer)COVID-19–specific risk factors (according to the Swiss Federal Office of Public Health) are additional exclusion criteria. In case of COVID-19–specific exclusion criteria, participation in the study will only be allowed when the patients’ treating physician provides written informed consent allowing participation in the study despite the presence of COVID-19–specific exclusion criteria. COVID-19–specific exclusion criteria include:High blood pressure (self-reported; systolic ≥140 mm Hg or diastolic ≥90 mm Hg)Chronic respiratory conditionUncontrolled type 2 diabetesCondition or therapy that weakens the immune systemUnstable cardiovascular diseaseCancer (present or under treatment)Serious obesity (BMI≥40 kg/m^2^)

### Interventions

#### Control Group

The control group will proceed with the usual care provided by the (memory) clinics where the patients are recruited. As described in section “Introduction—Choice of comparators” and based on clinical practice guidelines [90], in Switzerland, usual care is highly individual, varies between (memory) clinics where patients are recruited, and it is unclear whether patients comply with the recommendations of their clinicians. Therefore, details about all structured or guided usual care activities or both, as well as medication intake, will be assessed in both the intervention and control groups. If there are relevant between-group differences in usual care, these differences will be accounted for in the analysis and discussion of results.

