### Explanation and Choice of Comparators

According to a recent systematic review summarizing worldwide available clinical practice guidelines and consensus statements, recommendations for the treatment and management of individuals with mNCD can be classified into 4 categories: interventions for risk reduction, pharmacological interventions, nonpharmacologic interventions, and counseling. Recommendations for nonpharmacological interventions mainly include physical and cognitive activity interventions; however, the specific training characteristics (eg, frequency, intensity, type, volume, and progression) are not specified [90].

In line with these recommendations, in Switzerland, usual care for mNCD typically includes treating medical conditions other than mNCD (eg, diabetes mellitus and depressive symptoms), controlling comorbidities (eg, hypertension and obesity), and managing risk factors (eg, smoking habits and physical and cognitive inactivity). In this regard, usual care may include medication, recommendations for changing lifestyle habits (eg, living a cognitively, physically, and socially active life), physiotherapy to treat specific health problems, such as back pain or mobility problems, occupational therapy, or day clinic visits. This justifies the selection of usual care as the control intervention.

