After recruitment and providing written informed consent (see section “Methods—Recruitment”), participants will be screened on eligibility (see section “Methods—Eligibility Criteria”), and premeasurements will be scheduled for all eligible participants. Pre- and postintervention measurements will take place within 2 weeks before starting and after completing the intervention. For participants recruited in Zurich, preintervention measurements will take place at ETH Hönggerberg ([name]). For participants recruited in St. Gallen, premeasurements will take place at the Eastern Switzerland University of Applied Sciences ([name]). The measurements will take approximately 90 minutes. For all participants with no contraindications to magnetic resonance imaging (MRI), an additional appointment to conduct an MRI scan (duration: approximately 1 hour [including preparation]) at University Hospital Zurich ([name]) will be scheduled. All measurements will be led by 2 investigators from our research team trained in the application of the measurement techniques and protocols. Pre- and postintervention measurements will be scheduled to occur at approximately the same time of the day (±2 h) for each participant. To minimize the influence of transient confounding effects on HRV, all participants will additionally be instructed verbally and in writing to follow a normal sleep routine the day before the experiment, to avoid intense physical activity and alcohol consumption within 24 hours before measurements, and to refrain from coffee–or caffeinated drinks as well as food consumption at least 2 hours before measurements [95]. After completing premeasurements, participants will be randomly allocated to the intervention or control group and will be instructed about their respective intervention procedures (see section “Methods—Interventions”). For participants in the intervention group, the exergame device will be installed in their homes; they will receive safety instructions and will be familiarized with the exergame training system. Subsequently, the study intervention will be started (see section “Methods—Interventions—Intervention Group”). After completing the 12-week intervention period, postintervention measurements will be performed for both groups. No compensation will be granted to the participants, but detailed feedback on individual performance as well as the study outcomes in general will be provided at the end of the trial. Figure 1 summarizes the study procedures.

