##### Baseline Factors

Baseline factors are collected through demographic data, including age, sex, height, weight, BMI, years of education, physical activity behavior (ie, measured with the German version of the International Physical Activity Questionnaire Short Form—short form [190,191] and analyzed according to published guidelines for data processing and analysis of International Physical Activity Questionnaire Short Form—short form [192]), clinical subtype (ie, mNCD due to AD, mild Frontotemporal NCD, mNCD with Lewy Bodies, or mild vascular NCD), medication intake, and changes in medication intake between pre- and postintervention measurements.

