### Blinding

Outcome evaluators of pre- and postintervention measurements will be blinded to the group allocation (single blinding). To ensure blinding and blind-keeping of outcome assessors, detailed study-specific guidelines for all relevant procedures related to blinding and blind-keeping of outcome assessors have been established, which will be followed by all involved study investigators. For data assessed throughout the intervention period (ie, only applicable to the intervention group), blinding of investigators is not possible. The blinding of participants will also not be possible because usual care will be used as a control intervention.

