### Statistical Methods

Statistical analysis will be executed using R (The R Foundation), in line with RStudio (RStudio Inc). For demographics as well as training adherence and compliance, all collected data will be included (ie, including data of dropouts up to the time point of their withdrawal). For primary and all secondary outcomes, the data of all participants who completed pre- and postintervention measurements, regardless of protocol adherence, will be included in the statistical analyses. Questionnaire scores will be regarded as ordinal data. Data will be reported as mean (SD) values for continuous parametric data and median (IQR) values for continuous nonparametric data.

For all outcomes, descriptive statistics will be computed first. Normality distribution of data will be checked using the Shapiro-Wilk test. The level of significance will be set to *P*≤.05 (2-sided, uncorrected).

For all demographic variables, between-group differences (ie, intervention vs control) will be tested using an independent *t* test or Mann-Whitney *U* test in case the data are not normally distributed. For primary and secondary outcomes, the assumption of homogeneity of variance will be checked using Levene test. In case all assumptions for a 2-way analysis of covariance (ANCOVA) are met, effectiveness of the “Brain-IT” training will be analyzed using a two-way ANCOVA with the premeasurement value as covariate for the predicting group factor and the postmeasurement value as outcome variable [202]. If not all assumptions are met, the Quade nonparametric ANCOVA will be used. Because of the stratification by sex in the randomization process, no sex-specific statistical analysis will be computed. However, if there are relevant between-group differences in sex distribution or other demographic variables, these will be included in the statistical analyses as additional covariates. To determine whether the effects are substantive, partial eta-squared (η^2^_p_) effect sizes will be calculated for all primary and secondary outcomes. Effect sizes will be interpreted as small (0.01≤η^2^_p_<0.06), medium (0.06≤η^2^_p_<0.14), or large (η^2^_p_>0.14) [203].

Statistical analysis will be performed by PM after data collection is completed. As this is a small-scale RCT, no interim analysis will be performed.

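### The rule to account for between-group differences in usual care is not limited to care recorded before randomisation, so it can bias the estimated effect of adding Brain-IT

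*Protocol article*

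**What the plan says.** The Control Group section explains that usual care is individual and varies between clinics, and that "it is unclear whether patients comply with the recommendations of their clinicians". For that reason, details of structured or guided care, "as well as medication intake, will be assessed in both the intervention and control groups". The rule then follows: "If there are relevant between-group differences in usual care, these differences will be accounted for in the analysis and discussion of results". No method, threshold or time point is given.

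Four other places bear on how this rule would work:

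- **Trial Design and Study Setting:** "After completing premeasurements, participants will be randomly allocated to the intervention or control group".
- **Blinding:** outcome assessors are blinded, but "The blinding of participants will also not be possible because usual care will be used as a control intervention".
- **Baseline Factors:** the list, described as collected with the demographic data, ends with "changes in medication intake between pre- and postintervention measurements".
- **Statistical Methods:** the model is an ANCOVA on the postmeasurement value with the premeasurement value as covariate. It adds that "if there are relevant between-group differences in sex distribution or other demographic variables, these will be included", and says they enter as additional covariates.

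The hypothesis in Objectives and Hypotheses compares Brain-IT added to usual care with usual care alone.

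**The concern.** Care received during the 12 weeks comes after allocation. Usual care as described under Explanation and Choice of Comparators includes physiotherapy, occupational therapy, day clinic visits and advice to stay cognitively, physically and socially active. Participants who know they have been given 120 minutes of training a week may drop some of this, and controls may take up more. Usual care is also self-reported (Limitations), so reporting may differ by arm even where behaviour does not.

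A difference in care that allocation causes is part of the effect the hypothesis asks about. A model that conditions on it estimates something else. The trigger is also data-dependent, because whether a difference is relevant is judged after the groups have been compared. The trial's stated purpose is to supply a treatment effect estimate for sizing a full-scale trial, so an error here would carry forward into that design.

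**Working it through.** The plan gives no figure on this point, so there is none to reproduce. The check has two parts.

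**1. What the text permits**

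- *Timing.* Randomisation follows the premeasurements. Medication change from pre to post is therefore post-randomisation by definition. For usual-care activities the timing is implied, not dated: care is assessed in both allocated groups, and compliance with advice is part of the reason for recording it.
- *Timeline table.* Table 3 has no row for usual care and ticks baseline factors only at premeasurement, when a pre-to-post medication change cannot yet be known.
- *Method.* The phrase in the Control Group section names none. The one method the article states for imbalances between groups is to add covariates (Statistical Methods).
- *Limits.* Nothing confines the rule to premeasurement values or to a secondary analysis.

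**2. What adjustment could do to the estimate**

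The total effect is set to 0.5, the SMD anticipated under Sample Size. All other inputs are assumptions. Let *a* be the effect of allocation on on-trial usual care (or on its self-report) and *b* the effect of usual care on the outcome, both in units of about one standard deviation. If usual care and outcome share no unmeasured cause:

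adjusted effect = 0.5 − *a* × *b*

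| *a* | *b* | Calculation | Adjusted effect |
|---|---|---|---|
| 0 | any | 0.5 − 0 | 0.50 |
| −0.3 | 0.2 | 0.5 + 0.06 | 0.56 |
| +0.3 | 0.2 | 0.5 − 0.06 | 0.44 |
| −0.5 | 0.4 | 0.5 + 0.20 | 0.70 |
| +0.5 | 0.4 | 0.5 − 0.20 | 0.30 |

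Suppose instead that usual care has no effect on the outcome (*b* = 0), but an unmeasured factor raises usual care by 0.4 and lowers the outcome by 0.4. The within-arm slope of outcome on usual care is (0.4 × −0.4)/(1 + 0.4²) = −0.16/1.16 = −0.138. The adjusted effect is 0.5 + 0.138 × *a*, which is 0.43 for *a* = −0.5 and 0.57 for *a* = +0.5.

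Large-sample simulation agreed with these values. The model with the premeasurement value as its only covariate returned 0.50 in every scenario.

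The conditional rule was simulated with 14 per arm, *b* = 0.4, no common cause, and adjustment only when the observed imbalance in usual care was at least 0.5 SD (an assumed trigger):

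| *a* | Rule fires | Mean estimate under the rule | Mean unadjusted |
|---|---|---|---|
| 0 | 20% | 0.50 | 0.50 |
| −0.5 | 52% | 0.66 | 0.50 |
| +0.5 | 51% | 0.34 | 0.50 |

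The standard deviation of the unadjusted estimate was about 0.28. A shift of 0.06 is small against that (0.06/0.28 = 0.21). A shift of 0.16 is not (0.16/0.28 = 0.57).

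**The case against.** The best defence is that the sentence is loose and need not mean what is feared. Its stated motive, that care is individual and differs between clinics, describes variation that exists before randomisation, and adjusting for usual care recorded then would be harmless. No covariate adjustment of the primary model is announced. The Statistical Methods section provides extra covariates for sex and demographic variables and does not mention usual care. Accounting for a difference could mean a sensitivity analysis or a by-arm table. Both arms are to continue usual care, and nothing shows that training displaces it. With 17 to 20 recruited per arm, chance imbalance is also a likely source of any difference. In the no-link simulation, adjusting caused no bias and slightly reduced the spread of the estimate (0.275 to 0.252). The trial is exploratory and says it will probably be underpowered.

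Much of this stands. It makes the problem conditional, and it rules out some stronger readings:

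- A reader might infer that the plan definitely adjusts the primary model for post-randomisation care. The text permits this but does not state it.
- A reader might call the trial open-label. It is single-blinded with blinded outcome assessors; only the participants' knowledge of their arm matters here.
- A reader might conclude that the demographic-covariate rule will bring medication change into the model. The Baseline Factors wording leaves that possible, but treating a pre-to-post change as a demographic variable is strained, and the point does not depend on it.

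The defence does not remove the rule itself. The article commits to using these differences in the analysis, without a limit on timing or on the status of that analysis. That is a stated rule, not a detail left for later, and a sound analysis plan would have to narrow it. The observed data cannot show whether a difference arose by chance or through allocation.

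**Conclusion.** The point holds in conditional form. As written, the plan allows a data-triggered adjustment for care that follows randomisation, in participants who know their allocation. Such adjustment can bias the estimate of Brain-IT added to usual care versus usual care. It does so if three things hold together: the usual care adjusted for is post-randomisation (explicit for medication change, implied for activities), it enters as a covariate, and allocation has altered usual care or its self-report. If allocation alters neither, there is no bias.

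Neither direction nor size can be determined from the documents. The illustrative range of 0.30 to 0.70 around a true 0.5 rests entirely on the assumed *a* and *b*. For the same reason, a reader might be tempted to express the bias as a share of the 3-point Qmci change taken as clinically meaningful, but no passage supplies the inputs for that.

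**What to change.** In the Control Group and Statistical Methods sections:

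1. State that the primary and secondary ANCOVA models, and the Quade alternative, are not adjusted for usual care, medication or medication change arising after randomisation.
2. Summarise these by arm.
3. Allow usual care as a covariate only at its premeasurement level, named in advance, and say when usual care is recorded.
4. Label any analysis using post-randomisation usual care as an exploratory sensitivity analysis.
5. In Other Endpoints, list pre-to-post medication change outside the baseline factors.

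The cost is wording. Data already planned stay the same, unless a premeasurement covariate is wanted and usual care is not at present recorded at that visit. The downside is that a chance imbalance in on-trial usual care is handled only descriptively or in the sensitivity analysis, and any precision gained by adjusting for it is given up.

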#### Intervention Group

Participants in the intervention group will perform a 12-week training intervention in addition to their usual care (as provided by the [memory] clinics where patients were recruited). The training will be prescribed according our “Brain-IT” training concept. This motor-cognitive training concept represents a guideline for applying exergame-based motor-cognitive training by standardizing the training characteristics (eg, training frequency, intensity, and duration) as well as the structure and content of the training, whereas the exergame device and the specific games used within each of the defined neurocognitive domains can be replaced by alternative exergames. In this project, our training concept was implemented using the “Senso (Flex)” (Dividat AG). This platform was found to be suitable for the “Brain-IT” training [87] and is a widely used means for motor-cognitive training within geriatric populations, physiotherapy, and rehabilitation in Switzerland. The original “Brain-IT” training concept has recently been published with sufficient detail about the exergame components as well as the exercise and training characteristics (ie, including all predefined levels of task demands as well as the detailed progression rules) to allow full replication (ie, consider supplementary file 3 of [89]). Some minor modifications were implemented in the “Brain-IT” training concept for use in this study, based on the findings of our pilot feasibility RCT (under peer review; registered at ClinicalTrials.gov NCT04996654). This will be complemented in cases in which suitable new games become available throughout the study. The final (modified) “Brain-IT” training concept will be published with the manuscript reporting the results of this study, and will additionally provide specific information that would theoretically allow adaptation of the training to other hardware and software solutions. To ensure replicability, the “Brain-IT” training concept was planned and will be reported using the Consensus on Exercise Reporting Template [98].

For an overview, the “Brain-IT” training concept consists of individually adapted multidomain exergame–based simultaneous motor-cognitive training with incorporated cognitive tasks that is adopted with a deficit-oriented focus on the neurocognitive domains of (1) learning and memory, (2) executive function, (3) complex attention, and (4) visuospatial skills. Each participant is instructed to train 5 times per week for 24 minutes per session, resulting in a weekly training volume of 120 minutes. All training sessions are planned to take place at participant’s homes using the “Senso Flex” hardware (Dividat AG; CE certification pending; see left side of Figure 2). The “Senso Flex” is a home-based version of the “Senso” (Dividat AG; CE certification; see right side of Figure 2). It consists of a 1.11×0.99 m rollable mat that is plugged into a portable computer and a frontal television (or other screen) at home. Both systems divide the pressure-sensitive stepping area into five fields: (1) center (home position), (2) front, (3) right, (4) back, and (5) left. The device detects the participants’ position and timing of movements to interact with different game scenarios programmed in the training software. Weight shifting, walking on the spot, and steps in 4 directions (ie, front, right, back, and left) enable interaction with and control of the exergame scenarios displayed on a frontal screen. Visual, auditory, and somatosensory (vibrating platform; only available on the “Senso”) feedback is provided in real time to enrich the game experience. Various games are available for training different neurocognitive domains (more details on how the device is implemented in our training concept have been provided [89]).

Adherence to the training will be monitored (see section “Outcomes—Other Outcomes—For the intervention group,” ie, exergame training), and participants will be actively motivated and reminded to adhere to the training by the person responsible for supervision and correspondence with the respective study participant. Upon the request of participants, training can be paused for a maximum of 2 weeks (eg, because of holidays).

